### **7.3 Sample Size Estimation**

This study will test the hypothesis that the success rate of diagnostic cerebral angiography by TRA approach is not inferior to that by TFA approach.

We assume the success rates of diagnostic cerebral angiography by TRA and TFA are 97% and 98% respectively by considering the data in the references, with a margin for non-inferiority of -5%, a power of 90% at one-side significance level of 0.025, and a drop-out rate of 10%, 429 cases are needed for each group according to PASS 15 software, and thus a total of 858 subjects need to be enrolled in this study.

### **7.4 Datasets for Analysis**

The following datasets will be established for analysis in this study:

Full Analysis Set (FAS): The FAS will include subjects randomized to receive TRA or TFA cerebral angiography, with recorded evaluation results of the diagnosis. The effectiveness will be analyzed mainly based on FAS by group of randomization.

Safety Set (SS): The SS will include all subjects randomized to receive cerebral angiography via TRA approach or TFA approach. This analysis will be performed by group of subjects based on their actually received diagnostic procedures.

Per Protocol Set (PPS): PPS is a subset of the FAS, including subjects from the FAS with no major protocol deviations. The criteria for major protocol deviations should be finalized before the lock of the database, and the lists of subjects to be included and excluded from the PPS should be reviewed and discussed by the principal investigator, the statistician, and the sponsor at the data review meeting before the lock of the database.

### **7.5 Handling of Missing Data**

Missing data will not be imputed in this study.

### **7.6 Safety Analysis**

Safety will be analyzed based on the SS.

#### **7.6.1 Adverse Events (AEs)**

For adverse events (AE), only treatment emergent adverse events (TEAE) will be summarized in this study, which is defined as: any adverse event that occurs during or within 30 days after the angiography. AEs will be coded using MedDRA 24.1 or higher version.

Frequency tables will be used to summarize TEAEs based on incidences by system organ class (SOC) and preferred term (PT) for each group in descending order, unless otherwise specified. If a subject experienced more than one adverse events in the same SOC or PT, only the one with the highest severity will be counted.

TEAEs of the following categories will be summarized:

- All TEAEs, and all angiography related TEAEs
- Moderate and severe TEAEs, and angiography related moderate and severe TEAEs
- Treatment emergent serious adverse events (SAE), and angiography related SAEs

Angiography related TEAEs including those with a definite, possible, indeterminate, or missing correlation to the angiography.

The incidences of angiographic complications during and within 24 hours after the procedure will be separately summarized by type (pathway-associated complications/neurological complications) and by severity (severe/mild).

#### **7.6.2 Death**

The rate of death within 30 days after the procedure and rate of angiography related death within 30 days after the procedure will be summarized, and a list of deaths of the subjects will be provided.

## **7.7 Effectiveness Analysis**

The effectiveness will be analyzed based on FAS and PPS, and FAS will be used as the main dataset for effectiveness analysis.

### **7.7.1 Primary Effectiveness Analysis**

The primary effectiveness endpoint of this study is the success rate of diagnostic cerebral angiography, which is defined as the aortic arch vessel is successfully selected without changing the puncture site, with angiography results meeting the diagnostic requirements. Any change of puncture site before or during the procedure after a subject has been randomized would be treated as a diagnosis failure.

The success rate and failure rate of diagnosis will be described, and the causes of failure will be summarized (see Section 2.2 Study Endpoints for details). The Clopper-Pearson method will be used to calculate the 95% confidence intervals (CI) for rate of successful diagnosis in both groups, as well as the difference in rates between the two groups and its 95% CI (Miettinen-Nurminen method). Chi-square tests will be used for non-inferiority tests for rates of successful diagnosis in both groups, and Logistic regression will be used to calculate odds ratio (OR) between the two groups and its 95% CI.

### **7.7.2 Analysis on Secondary Effectiveness Endpoints**

A statistical description of rate of successful accurate diagnosis, duration of angiography, duration of fluoroscopy, flat time and VAS score will be provided, and the linear mixed model will be used to calculate the differences between groups and their 95% CIs using group as covariate and study center as random effect.

### **7.7.3 Exploratory Analysis**

If data permit, Logistic regression will be used to conduct an exploratory analysis of factors affecting cerebral angiography through TRA approach. Influencing factors may include age, diabetes, hypertension, hyperlipidemia, smoking history, Type III aortic arch configuration, looping technique, diameter and development status of the radial artery, development status of the aortic arch and arch vessels and degree of tortuosity, previous history of surgery on the radial artery.

## **8. Data Management**

All subject information, medical records, and laboratory data must be kept confidential.

The information and data will be discussed, analyzed and reported only for the purpose of this clinical study. Subject number will be used in the electronic case report form and any other report to identify the subject, and subject's identity will be kept confidential.

### **8.1 Completion of Case Report Form**

The Case report Form (CRF) will ensure that all data required in the protocol and meeting the requirements for statistical analysis will be collected. The Electronic Case Report Form (eCRF) is an electronic form of the CRF, to record the study relevant data of each subject. The electronic case report form is required to be completed for all enrolled subjects.

Electronic Data Capture System (EDC) will be used for data acquisition and management in this study. The investigator or Clinical Research Coordinator (CRC) should fill in the eCRF accurately, timely, completely as required according to the CRF filling guidelines.

### **8.2 Data Verification and Query**

Both automatic edit check and manual edit check will be conducted to ensure the integrity, consistency and accuracy of the study data. The EDC system will run real-time automatic logical verification for all filled data, for example, verification on the range of data values, and logical relations, etc. The data manager will send manual queries in the EDC.

### **8.3 Lock of the Database**

The data manager will lock the database after all data entered, all queries resolved, and the principal investigator, statistical analysis personnel, clinical data monitoring representatives and the data management person have jointly completed the final definition and judgment of the analysis population and given written permission on lock of database.

Generally, the database, after being locked, cannot be unlocked again. If unlock of the database is needed, the conditions and process for unlocking must comply with the corresponding SOP, and the unlocking process must be carefully controlled and recorded.

## **9. Ethical Protection and Informed Consent**

### **9.1 Ethical Considerations, Whether Involving Human Genetic Resources and Use of Highly Pathogenic Microorganisms**

This is a non-inferiority study to evaluate the safety and effectiveness of TRA and TFA angiography. This study involves no blood or tissue sample collection, and no additional follow-up costs will be incurred by the patients. This study will be conducted in compliance with *Measures for the Ethical Review of Biomedical Research Involving Humans* of China and international ethical guidelines such as the *Declaration of Helsinki*. This study does not involve the use of human genetic resources or highly pathogenic microorganisms.

## **9.2 Study Protocol Approval**

Before the clinical trial, the investigator should submit the study protocol, ICF and other relevant documents to the medical ethics committee of the hospital of the corresponding clinical trial institution. This study can only be initiated after being approved by the Ethics Committee. Any amendment to the protocol must be approved by the Ethics Committee before implementation.

## **9.3 Informed Consent Process and Informed Consent Form**

The investigator must explain the details of the clinical study to the subject before the enrollment of that subject:

The subjects' participation of this study should be voluntary and they have the right to withdraw at any stage of the clinical study;

Personal data of the subjects will be kept confidential. Representatives from the ethics committee, and drug and device administration authorities as well as the study team members may have access to the data of the subjects, but shall not make any of the data public;

During the clinical study, the clinical study institution is obligated to provide the subjects with the information related to the clinical study;

Subjects should be aware of the contents, purpose, possible adverse events and other relevant information of the study, and can only be enrolled after confirming that they fully understand the study and signed the informed consent form.

The informed consent form shall be signed by the investigator and the subject in duplicates, with one copy to be kept by each of them.

# **10. Stipulation on Adverse Events**

## **10.1 Adverse Events**

### **10.1.1 Definition of Adverse Events**

An AE is defined as any untoward medical occurrence during the course of the clinical trial. Only TEAEs will be summarized in this study, which is defined as any adverse event that occurs during or within 30 days after the angiography. AEs will be coded using MedDRA 24.1 or higher version.

TEAEs of the following categories will be summarized:

- All TEAEs, and all angiography related TEAEs
- Moderate or severe TEAEs, and angiography related moderate or severe TEAEs
- Treatment emergent serious adverse events (SAE), and angiography related SAEs

Angiography related TEAEs including all TEAEs with a definite, possible, indeterminate, or missing causal relationship to the angiography.

#### **10.1.2 Severity of Adverse Events**

Mild: A mild AE is defined as any AE that can be tolerated by the subject, which does not affect the study treatment, requires no special treatment, and has no impact on the health of the subject.

Moderate: A moderate AE is defined as any AE that cannot be tolerated by the subject, and the device needs to be withdrawn or special treatment is needed, which has a direct impact on the health of the subject.

Severe: A severe AE is defined as any AE that endangers the life of the subject, results in death or disability, and requires immediate withdrawal of the device or emergency treatment.

#### **10.2 Serious Adverse Events**

A serious adverse event (SAE) is any untoward medical occurrence in the clinical trial which:

- 1) Result in death;
- 2) Results in life-threatening disease or injury;
- 3) Results in persistent disability/incapacity;
- 4) Requires inpatient hospitalization or prolongation of hospital stay;
- 5) Requires medical or surgical intervention to prevent persistent disability/incapacity;
- 6) Is a fetal distress, fetal death, or congenital abnormality or birth defect, etc.

Transient ischemic attack and brain infarction: Events such as intraoperative vascular wall plaque detachment, catheter thrombosis, and gas embolism can cause ischemic stroke. Prevention methods include: Give systemic heparinization to the subjects after

successful puncture to prevent thrombosis in the catheter wall. Superselective angiography should be performed in the order of the aortic arch, the great vessels of the arch and their branches, and do not allow the catheter or guidewire to exceed the vascular wall plaque, so as to prevent plaque rupture or mural thrombosis detachment. Carefully check and drain the catheter to ensure there is no air in it, so as prevent the occurrence of air embolism; Thrombolysis or mechanical embolectomy should be done based on the condition when a distal vessel embolism is confirmed. Hyperbaric oxygen therapy can be given when air embolism occurs.

**Cortical blindness:** Cortical blindness is characterized by loss of binocular vision, but with normal pupil reflex to light. Patients may be other symptoms such as amnesia, hemiplegia, and headache, etc., which is most commonly seen after vertebral arteriography, and other cerebrovascular or coronary arteriography. The pathogenesis is associated with cerebral vasospasm and destruction of blood-brain barrier, which may be a similar type of disease with reversible posterior leukoencephalopathy syndrome. There is no treatment with special effect for cortical blindness after cerebrovascular angiography, so it is necessary to improve the head imaging examination to exclude the posterior circulating cerebral embolism. Appropriate fluid replenishing can be used to promote the excretion of contrast agent, and antispasmodic drugs can be given at the same time. Cortical blindness usually has a good prognosis, with complete recovery within several hours or days.

**Artery dissection:** Dissection occurring in the femoral artery or iliac artery is usually not detected in time as the puncture needles, catheter and guidewire enters under the intima. The dissection is retrograde dissection which is not easy to continue to expand as the intima rupture is located in the distal segment of the vascular dissection while the vascular dissection is located in the proximal segment. Generally, it can heal by itself after a few hours or days. Blood supply to the contralateral great vessels may be affected if the vascular dissection extends too deeply, for which local angiography should be performed in time, and assistance from the surgery department should be requested if necessary. Arterial dissections occurring in the superior arch vessel are antegrade dissections, for which the interventional procedure should be suspended

immediately and angiography should be performed a few minutes later. No special treatment is needed if there is no significant lumen stenosis or significant contrast agent retention in the vessel wall. If the luminal flow is significantly affected, stent placement can be considered.

**Vasovagal reflex:** When the peripheral blood vessels are stimulated during the removal of the vascular sheath, hand pressure, or pressure by using bandage, patients may experience vagus reflex, which is mainly manifested as decreased blood pressure and heart rate. Vagus reflex symptoms such as cold sweat, pallor, and clammy limbs may also occur. For the elderly or cardiac insufficiency patients, vagal reflex can be life-threatening. Methods for treatment include relief of vascular irritation, intravenous injection of atropine, supplement of blood volume appropriately, and use of vasoactive drugs such as dopamine to increase blood pressure when necessary.

**Hematoma formation:** Inguinal hematoma is the most common complication of the puncture site. Causes include abnormal coagulation function or use of any anticoagulant drug; repeated puncture of the femoral artery during the procedure, or bilateral puncture of the femoral artery with its branches involved at the same time; inappropriate method or insufficient time of compression hemostasis at the puncture site of the femoral artery after the procedure, and symptoms that increasing abdominal pressure, such as severe cough, and constipation; and early weight-bearing activities of the lower limb of the puncture side. Prevention methods include: Confirm that the patient has no coagulation dysfunction before the procedure, and control the amount of heparin appropriately based on the time of the procedure; Minimize the number of femoral artery punctures; ensure the site of postoperative pressing is appropriate, and the time of pressing should be no less than 15 minutes; Ask the patient to avoid severe cough and keep flat in bed for at least 24 hours. Minor bleeding can be managed by mechanical compression. Most cases of hematomas are self-limiting and can be absorbed by the patients.

**Pseudoaneurysm:** After femoral artery puncture, blood can enter the perivascular tissue through the damaged wall and form a space, resulting in pseudoaneurysm. Systole causes arterial blood flowing through the neck to the lumen while diastole causes blood returning to the artery. Causes of pseudoaneurysm include: too many puncture times;

low puncture site and thin femoral artery results in relatively large puncture wound; more perivascular soft tissue, which makes compression hemostasis difficult; Large size of arterial sheath. Most pseudoaneurysms can be locally wrapped with pressure on the neck of the pseudoaneurysms under ultrasonic localization, and the cavity can be closed 3-5 days thereafter. For pseudoaneurysms for which compression occlusion is difficult, thrombin can be injected under ultrasound. In rare cases, the pseudoaneurysm can be occluded with drug coated stents, or surgically removed or repaired.

The incidence of neurological complications caused by cerebral angiography is low, and there is currently no direct evidence on the risk of neurological complications after TRA angiography. Multiple studies have shown that no serious neurological complications occur in the TRA or TFA group.

**10.4 Determination of Relationship Between Adverse Events and the Angiography Relationship with the angiography** (1) There is a reasonable temporal relationship between the two; (2) The event is a known risk of angiography, or can be explained by the mechanism of angiography; (3) The event is relieved or disappeared after stopping the angiography; (4) The event reappears after reuse of angiography; (5) The event could not be explained by other contributing factors. Any event that meets all of the five items above will be considered as "definitely related" to the angiography; while any event meeting two of the above items will be considered as "possibly related" to the angiography.

Unrelated to the angiography: (1) There is no reasonable temporal relationship between the two; (2) This type of the adverse event is not possible to be caused by the angiography; (3) The adverse event can be explained by the concomitant use of any device/drug, subject's disease progression, or other treatment effects. Any event meeting three of the above items will be considered as "definitely unrelated" to the angiography; while any event meeting one of the above items will be considered as "unlikely related" to the angiography.

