| Effectiveness endpoints f                      |                               | X        |                              |                                          |
| VAS score                                                 |                               |          | X                            |                                          |
| Angiographic complications (Angiography associated TEAEs) |                               | X        |                              |                                          |
| Other TEAEs                                               |                               | X        |                              |                                          |
| Concomitant medications/treatments                        |                               | X        |                              |                                          |

- a The screening visit and baseline visit may be on the same day;
- b The time window for V3 is  $\pm 7$  days, for which telephone follow-up is acceptable.
- c Measurements for vital signs include blood pressure and heart rate;
- d Blood routine test (red blood cells, white blood cells, platelet count, and hemoglobin), renal function test (Cr), coagulation function test (APTT and INR), and urine HCG test (only for women of child bearing potential);
- e Examination in the screening period will be vascular ultrasound or CTA of the four extremities, to evaluate the vascular conditions of the subjects, for which results within 90 days prior to informed consent are acceptable; while the corresponding examination within 24 hours after the procedure will be Vascular ultrasound of the puncture site, to evaluate the conditions of arterial occlusion.
- f Effectiveness endpoints include rate of successful diagnostic angiography, rate of successful accurate diagnosis, duration of angiography, duration of fluoroscopy, flat time and VAS score. VAS score will be completed within 24 hours after the procedure, and other items should be done as soon as possible after the procedure.
- g The laboratory test and preoperative and postoperative ultrasonography during the screening period of this study are parts of the routine diagnosis and treatment in clinical practice, which will not cause additional burden to the patients.

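### The causality rule in protocol 10.4 can label one event both possibly and unlikely related to the angiography, so the descriptive counts of related events are not fixed for such events

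*Combined protocol and SAP*

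**What the plan says.** Protocol 10.4 lists five items that support a relationship: a reasonable time relation, a known risk or mechanism, "3) The event is relieved or disappeared after stopping the angiography", and then "4) The event reappears after reuse of angiography; (5) The event could not be explained by other contributing factors". Two thresholds follow: "Any event that meets all of the five items above will be considered as 'definitely related' to the angiography", and "any event meeting two of the above items will be considered as 'possibly related' to the angiography".

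A separate list has three items against a relationship: no reasonable time relation, an event that angiography could not have caused, and an explanation by a concomitant device or drug, disease progression or another treatment. All three give *definitely unrelated*. For *unlikely related* the wording is "while any event meeting one of the above items will be considered as" that label.

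Protocol 7.6.1 sets the counting rule: "Angiography related TEAEs including those with a definite, possible, indeterminate, or missing correlation to the angiography". Protocol 10.1.1 and SAP 9.2.1 repeat it in substance. *Unlikely related* is not among the counted labels. The planned outputs that use it are related TEAEs, related moderate and severe TEAEs and related SAEs (protocol 7.6.1, SAP Table 6). Protocol 7.6.2 and SAP 9.2.2 add deaths: the "rate of angiography related death within 30 days after the procedure will be summarized".

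**The concern.** The two lists are scored separately, and nothing says which result prevails when both thresholds are reached. The two labels fall on opposite sides of the counting line, so the same facts can put an event inside or outside the related tables.

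The protocol's own examples fall into the overlap. Brain infarction is a listed procedural risk in 10.3, and in patients referred for cerebral angiography their disease may also explain it. Groin hematoma is described in 10.3 as the most frequent puncture-site complication, with anticoagulant use among its causes. Protocol 5.2 places no limit on concomitant drugs. At stake is whether two assessors with the same record would produce the same tables of related events.

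Two lesser gaps accompany this. *Definitely related* requires recurrence on re-exposure, yet Appendix 1 schedules one study angiography. And *indeterminate* is counted as related, although 10.4 has no route to it.

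**Working it through.** The plan states no figure here to reproduce; the check is logical.

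**Inputs (protocol 10.4).** Let R1 to R5 be 1 if the corresponding related item is met, and U1 to U3 be 1 if the corresponding unrelated item is met. Let R = R1+R2+R3+R4+R5 and U = U1+U2+U3.

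- *Definitely related*: R = 5.
- *Possibly related*: R at two. The text does not say exactly or at least.
- *Unlikely related*: U at one, with the same ambiguity.
- *Definitely unrelated*: U = 3.

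**The realistic case.** The time relation fits (R1 = 1), the risk is known (R2 = 1), and disease or a drug could also explain the event (U3 = 1, hence R5 = 0). There is no relief on stopping (R3 = 0) and no re-exposure (R4 = 0). Then R = 1+1+0+0+0 = 2, which is *possibly related* and counted. Also U = 0+0+1 = 1, which is *unlikely related* and not counted. Both labels apply whether the thresholds mean exactly or at least.

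**All patterns.** Assume U1 = 1−R1, U2 = 1−R2, U3 = 1−R5, and R4 = 0. The free items are R1, R2, R3 and R5, so there are 2⁴ = 16 patterns.

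| Result | At least | Exactly |
|---|---|---|
| Both possibly and unlikely | 9 | 3 |
| Possibly only | 2 | 3 |
| Unlikely only | 3 | 3 |
| Definitely unrelated | 2 | 2 |
| No label | 0 | 5 |
| Definitely related | 0 | 0 |
| Total | 16 | 16 |

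**Item 3 not met** (as for any death): 2³ = 8 patterns. Three carry both labels on either reading. On the exact reading 4 carry none and 1 carries a single label (3+4+1 = 8). The three double-label patterns are (R1,R2,R5) = (1,1,0), (1,0,1) and (0,1,1). The second needs a well-timed, otherwise unexplained event that angiography could not cause. The third needs a known-risk event with no time relation. Only (1,1,0) is realistic.

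**Weaker link between the lists.** An event can fail to be a known risk without being impossible. If U1 = 1−R1 still holds, but U2 = 1 only excludes R2 = 1 and U3 = 1 only excludes R5 = 1, there are 36 patterns. Both labels appear in 13 (at least) or 7 (exactly). On the at-least reading one of the 36 has no label: only the time relation is met and no unrelated item is.

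**Effect of the empty top category.** Definite and possible are pooled by the counting rule, so moving an event between them changes no related count.

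**The case against.** The strongest case on the other side is that this is a wording flaw affecting descriptive tables. SAP Table 6 lists no test or between-group estimate for related events. Counting runs on the recorded label, so each event will have some status, and a missing label is counted as related. An independent clinical event committee evaluates safety events (protocol 11.6); its constitution is not in the documents and may set a precedence. All of this stands. It limits the consequence but does not remove the contradiction in 10.4, and the SAP supplies no tie-break.

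A reader might infer more than the documents support:

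- *That the 24-hour complication endpoints depend on this rule.* Appendix 1 has a row reading "Angiographic complications (Angiography associated TEAEs)", but that is only a schedule label. Protocol 2.2 and SAP 9.2.1 define those endpoints by a list of events, a time window and consequences, not by causality.
- *That the unreachable definite category distorts counts.* It does not, because of the pooling. Nor is it strictly impossible to reach: the exclusion criteria speak of a first study angiography, and 10.3 has angiography performed some minutes after an arch-vessel dissection. Re-exposure is off schedule and rare, not excluded.
- *That 9 of 16 is a share of events.* It counts logical combinations and says nothing about their frequency.
- *That the clearest case gets no label.* This needs two to mean exactly two. On the ordinary at-least reading, such an event is *possibly related* and counted.
- *That knowledge of the arm will bias the result.* The rule judges relation to angiography, which both arms undergo. The looseness leaves room for such an influence, but nothing in the documents shows a direction or size.

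**Conclusion.** The concern holds for one overlap. An event with a fitting time course and a known angiographic risk, which disease progression or a concomitant drug could also explain, is both *possibly* and *unlikely related*, with no precedence. For such events 10.4 does not fix the descriptive counts of related TEAEs, related SAEs and related deaths. The primary endpoint and the counts of all TEAEs, all SAEs and all deaths do not use the rule.

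The number of events affected cannot be derived from the documents. The realistic case rests on no assumption about how the two lists mirror each other beyond the obvious one, that an event with another explanation is not unexplained. The pattern totals do rest on the stated link between the lists and on no re-exposure. The conclusion would soften if the committee's constitution already contains a precedence rule; it would then only need to be cited. This should be corrected before database lock but does not threaten the trial's main conclusion.

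**What to change.** Reword protocol 10.4 so that every event gets exactly one label:

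1. Assess the related items first. Treat recurrence on re-exposure as applying only where it occurred, not as required for *definitely related*. Keep item 3 wherever it can be assessed: spasm or a vasovagal reaction can resolve once the stimulus stops, and dropping the item would move some events out of the related count.
2. All applicable related items met gives *definitely related*; otherwise, at least two gives *possibly related*.
3. State that *possibly related* prevails over *unlikely related* when both thresholds are reached.
4. With fewer than two related items, use the unrelated list: all three gives *definitely unrelated*, one or two gives *unlikely related*.
5. Define *indeterminate* as not assessable, and place there any event that reaches no threshold on either list.

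In the 16 patterns above, with item 3 assessable, this gives 1 definite, 10 possible, 3 unlikely and 2 definitely unrelated (1+10+3+2 = 16), with no double and no empty labels. The single unlabelled pattern under the weaker link falls to step 5.

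Repeat or cite the rule in SAP 9.2.1. Before database lock, have the clinical event committee apply it to events with conflicting or no labels, without knowledge of the arm where feasible. The cost is a rewording, a limited re-review of graded events, and a slightly higher related-event count. The documents do not show that item-by-item answers were recorded, so the committee may have to work from the event records.
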